# Body, Soul and Spirit, an adaptation of two evidence-based interventions to promote physical activity and healthy eating among adults in churches in Lagos Nigeria: a three-arm cluster randomized controlled pilot trial

**DOI:** 10.1186/s40814-020-00600-6

**Published:** 2020-05-07

**Keywords:** Physical activity, Healthy food, Fruit and vegetable, Church, Cultural adaptation, Community-based

## Abstract

**Background:**

Physical inactivity and unhealthy eating are two leading behavioral risk factors contributing to preventable non-communicable diseases (NCDs). Evidence-based interventions (EBI) using community-engaged approaches to address these risks abound in high-income countries. Comparatively, evidence of such interventions is sparse in low- and middle-income countries, where NCD mortality is greater. This paper describes the protocol for the development of the cultural adaptation and pilot testing of a combination of two EBI (i.e., Body and Soul and the Healthy Body Healthy Spirit), in church-based settings in Lagos, Nigeria. In addition, we describe the development of the inclusion of an additional component, i.e., faith-based text messages, into one of the treatment arms. Our objective is to assess the feasibility of developing and implementing the adapted interventions with the ultimate aim of developing a fully powered trial.

**Methods:**

This pilot study will assess the design and implementation of a three-arm cluster-randomized pilot trial in 12 randomly selected Anglican churches (4 in each arm). First, we will design a cultural adaptation of the two EBI’s to form a multifaceted combined intervention known as the *Body Soul and Spirit*. The second treatment arm, i.e., *Body Soul and Spirit Plus*, will retain all the components of *Body Soul and Spirit* with the inclusion of faith-based text messages using mobile phones. Participants in the control arm will receive information leaflets designed to increase physical activity and healthy food consumption. The outcome measures include participant recruitment and retention, program participation and satisfaction, and data collection completion rates. The outcomes for the proposed definitive trial will be the number of servings of fruit and vegetables and minutes of moderate to vigorous physical activity per day will be assessed at baseline, 3 and 6-month follow-up. Implementation outcomes will be assessed using qualitative and quantitative methods.

**Discussion:**

The study will enhance the understanding of how best to design and implement behavioral interventions in church-based settings using community-based participatory approaches. It will also inform the development of a definitive randomized controlled trial.

**Trial registration:**

Pan African Clinical Trials Registry on 12th July 2018. PACTR201807136835945. Available at https://pactr.samrc.ac.za/TrialDisplay.aspx?TrialID=3481

## Background

Globally, unhealthy diets and physical inactivity are important risks for non-communicable diseases (NCDs) particularly cardiovascular diseases (CVD), type 2 diabetes, and certain cancers [1]. Up to 2.7 million deaths are attributable to diets low in fruits and vegetables. Worldwide, low intake of fruits and vegetables is estimated to cause about 19% of gastrointestinal cancer, about 31% of coronary heart disease, and 11% of stroke [1]. Almost two million deaths (1.9 million) are attributable to physical inactivity. Physical inactivity and unhealthy diets are major contributors to high body mass indices, which ranks as a leading risk of death globally [1, 2].

In many low- and middle-income countries (LMICs), the prevalence of these risk factors is rising, particularly among adults in urban areas [3, 4]. Several African countries are undergoing rapid urbanization and an epidemiological transition with increased rates of NCDs, particularly cardiovascular diseases, diabetes mellitus, cancers, and obesity [5–8]. In Nigeria, almost one in five deaths is attributable to NCDs, and this rate is increasing [9]. National surveys indicate that the rate of overweight/obesity among women increased from 22% in 2008 to 25% in 2013 with the highest prevalence (44%) occurring in Lagos, the most populous city in Africa [10].

Although several evidence-based interventions (EBI) that address known NCD risk factors exist, they are often generated in high-income countries (HIC) and are not frequently deployed in low- and middle-income countries where a significant burden of NCD mortality and ill-health occur [11–13]. There is limited evidence to demonstrate if or how EBI generated in HIC may work in low- and middle-income country (LMIC) settings with different religious, socio-economic, and cultural environments. Research that comprehensively addresses effective ways of adapting evidence-based interventions generated in HIC into local contexts can significantly advance the field of NCD prevention and result in significant improvements in population health outcomes [14].

The vast majority of people in many sub-Saharan African nations are deeply committed to the practices and major tenets of either Christianity or Islam, which are the world’s two largest religions. Almost all (> 95%) Nigerians identify with at least one of these two religions [10, 15]. Religious environments play an important role in promoting physical activity and healthy eating [16, 17]. Not only are they potential points of contact among the populace, they also tend to hold regular events that involve food, relationships, and other activities. Churches, in particular, present a potentially effective channel for delivering health programs [18, 19]. However, the majority of existing church-based trials have been conducted in HIC like the USA and among minority groups (e.g., African Americans or Latinos), and few have targeted multiple risk behaviors. Interventions targeting multiple behaviors simultaneously have the potential to be efficient, cost-effective, and produce meaningful changes in population health [20, 21].

Mobile phone use has increased tremendously in Nigeria over the past 15 years. Nigeria ranks second, only to South Africa, with the highest proportion of mobile phone users in Africa [22, 23]. In 2019, there were over 172 million mobile subscribers, accounting for an estimated 87% of the population. This figure represented a 6.4% growth increase, compared to 162 million subscribers in 2017 [24]. This provides a window of opportunity to develop mobile phone interventions to promote physical activity (PA) and healthy food consumption (HFC) as has been done in some HICs. Previous studies in HIC have used mobile phone interventions to promote these behaviors. Of the potential approaches to mobile phones interventions, text messages hold great promise, because they can be tailored, are relatively low cost and have the ability to reach a large proportion of people without the need for an internet connection [25, 26]. Although evidence shows that text messages are effective for improving PA and HFC in HIC [27–31], few interventions have considered the use of faith-based text messages to improve or sustain the effect of such interventions in faith-based settings. Furthermore, none of these studies have been conducted in a highly religious LMIC like Nigeria.

The aim of this study is to assess the feasibility of developing and implementing a cultural adaptation of the effective components of two evidence-based interventions in church settings, i.e., Body and Soul [32] and the Healthy Body Healthy Spirit [33], to increase PA and HFC in a church-based LMIC setting, with the ultimate aim of developing a fully powered trial. We also aim to assess the process of developing and implementing faith-based text messages as a component of one of the treatment arms.

### Theoretical framework

As with the parent trials, we will be guided by the socio-ecologic theoretical model (Fig. 1) [34], which emphasizes the importance of the social environments that shape human behavior and addresses the personal, institutional, and community factors affecting them. The parent trials also emphasized the self-determination theory of motivation [35], which supports the intrinsic human tendency to behave in effective healthy ways.

**Fig. 1 Fig1:**
[figure not shown]
The socio-ecological theroretical model

A key aspect of this study involves the active participation of the community (church) members in its design and implementation. This is more likely to create sustainable interventions that promote community health [36]. In addition, this approach incorporates cultural norms and infuses community knowledge with evidence-based socio-behavioral theory for the effective implementation of complex health interventions [36, 37].

### Study objectives

Gather information from the church leadership and members and assess the process of using this information to develop a culturally adapted combined version of the two EBI and the additional faith-based text message component.Explore the acceptability of each of the adapted components of the original interventions from the perspectives of the church leadership and church members and assess the feasibility of implementing each intervention component.Assess the feasibility of recruitment and retention of the churches, church volunteers, and participants, assess consent rates and procedures, and gain estimates of recruitment and participation rates for the adapted interventionsDetermine the acceptability, feasibility, and accuracy (and factors influencing this) of the data collection methods and measures, assess data completeness and explore data missingness at 3 and 6 months follow-up and its implications in developing a fully powered trial.Assess the proportion of churches and study participants completing the culturally adapted intervention and explore factors that promote or discourage engagement with and completion of the intervention.Estimate key parameters like the effect sizes, intra-class correlation coefficients (ICC), and standard deviations and compare these with the values obtained in the literature to inform the calculation of an adequate sample size for a fully powered definitive trial.

## Methods

### Study setting

This study will be carried out in Lagos State, the commercial capital and a largely urbanized part of Nigeria. It will be conducted among churches in the diocese of Lagos Mainland of the Anglican Communion, Church of Nigeria. The diocese is headed by a bishop and has a total of 53 churches. A vicar, assisted by church priests, is responsible for overseeing the administrative and religious activities of each church. Each church has a governing council consisting of elected members. Church services are held primarily on Sundays with other religious activities occurring on other days of the week as needed. Each church has a medical committee, consisting of volunteers with interests in health-related matters. In addition, there is a diocesan medical committee that oversees health-related church activities of the entire diocese.

### Trial design

This is a pilot of a three-arm cluster randomized controlled trial and will be conducted in 12 (4 in each group) of the 53 churches in the diocese of Lagos Mainland of the Anglican Church of Nigeria. The twelve churches will be randomized into three arms as follows:
A.Body Soul and Spirit (BSS)B.Body Soul and Spirit Plus (BSS+)C.Usual care/control (Control)

### Participants

The study will be conducted among members of the participating churches in the diocese.

### Inclusion and exclusion criteria

To be eligible, participants must be adults aged 18 years or older who have been members of the church for at least 6 months and attend church services at least weekly. Eligible respondents for BSS+ must, in addition, have a text message-compatible mobile phone and have used it for at least 6 months. Acutely ill or disabled people will be excluded.

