**Intervention Component**	**Body and Soul**	**Healthy Body Healthy Spirit**	**BSS (Arm 1)**	**BSS plus (Arm 2)**	**Control (Arm 3)**
A cookbook with healthy eating recipes, cooking techniques, storage tips for fruits and vegetables (F&V), and health benefits of lowering fat/increasing F&V intake	✔	✔	✔	✔	
An exercise manual with biblical themes and scripture woven throughout		✔	✔	✔	
A workout audio CD containing local gospel music with biblical quotes and brief sound bites of pastor sermons spliced between songs		✔	✔	✔	
Public screenings of “Forgotten Miracles,” a video that targets fruit and vegetable intake using both spiritual and secular motivational messages	✔	✔	✔	✔	
Constitution of a project coordination committee	✔	✔	✔	✔	
Conduct at least one health event*	✔		✔	✔	
Motivational interviewing phone calls delivered to participants by trained volunteer peer counselors	✔	✔	✔	✔	
Churches will agree to implement at least one policy change^#^	✔		✔	✔	
Faith-based text messages				✔	
Distribution of information leaflets promoting physical activity and healthy food consumption			✔	✔	✔

*Examples of some of the events included in the parent trials were serving fruit and vegetables during the kick-off event, after church services, or at other church programs; sponsoring food demonstrations or taste tests; organizing tours of food markets for parishioners; inviting guest speakers; and having priest sermons related to health

^#^Potential policy changes include establishing guidelines for the types of foods served at church functions, changing snacks served at youth camps, or creating a food pantry

d) Supportive relationships

Motivational interviewing phone calls to selected church parishioners delivered by trained church volunteers [32, 33].

e) Policy change

Churches will agree to implement at least one policy change [32]. Potential policy changes include establishing guidelines for the types of foods served at church functions, changing snacks served at youth camps, or creating a food pantry.

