### Phases of the study

The study will be conducted in four phases.

*Phase 1—*Pre-implementation—Community entry, recruitment, and randomization of churches; partnership and capacity building; and needs assessment and situation analysis.

*Phase 2*—Intervention adaptation and development—Adaptation and design of the core components of BSS and BSS+ for use in a Nigerian setting.

*Phase 3*—Intervention implementation and delivery

*Phase 4*—Implementation evaluation—Data collection and analysis of implementation measures, study outcomes, and success criteria; calculation of an ICC, the means and variances for each the three treatment arms, effect sizes (all to potentially inform the sample size calculation in a full RCT), and the decision to determine whether or not to progress to a definitive trial.

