
### Sample size estimation

In a pilot trial, the objective is not necessarily to prove superiority of the treatment but to test trial procedures and processes and to obtain estimates of parameters for the main trial sample size calculation. Therefore, standard sample size formulae which are used for main treatment assessments are not usually applicable to pilot trials [62, 63] see Additional file 1. As recommended in the CONSORT guidelines for publishing protocols of pilot studies [62], we made a pragmatic decision to select 12 churches for the study and 25 participants per church based on our knowledge of the church structure, its demographics, and our pilot objectives.

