### Recruitment and retention strategies

Churches will make announcements for participation in the project, during church services, and using bulletin inserts or other usual means of communication. Trained church volunteers and/or research assistants will help to recruit interested participants. This will be based on participant eligibility and on a first-come, first-served basis. Recruited participants from each church will be selected to participate in the individual program activities and complete the surveys. Participant recruitment will be conducted in the three study arms in the same manner regardless of treatment allocation.

To promote participant retention, we will provide a small incentive (a gift worth $5 or less) to all participants regardless of the treatment arm. In addition, participants will receive at least two text messages and one phone call reminder to schedule a date for the follow-up surveys. We expect to be able to complete participant enrolment over a period of 12 weeks and will aim for at least 80% retention at the 6-month follow-up, noting any differences in attrition rates between study groups.

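### Phone possession is an eligibility criterion in BSS+ only, so both BSS+ contrasts compare phone owners with a mixed population

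*Protocol article*

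**What the plan says.** Under Inclusion and exclusion criteria, the protocol article sets common rules: "participants must be adults aged 18 years or older who have been members of the church for at least 6 months", with at least weekly attendance. It then adds a rule for one arm: "Eligible respondents for BSS+ must, in addition, have a text message-compatible mobile phone and have used it for at least 6 months". Nothing elsewhere extends this rule to BSS or control, and no comparison limited to owners and no adjustment for ownership is described.

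Phases of the study places these steps in Phase 1: "Community entry, recruitment, and randomization of churches; partnership and capacity building; and needs assessment and situation analysis". Individuals are recruited afterwards, by trained volunteers or research assistants, in order of arrival. Recruitment and retention strategies states: "Participant recruitment will be conducted in the three study arms in the same manner regardless of treatment allocation". The same section says that, to support follow-up, "participants will receive at least two text messages and one phone call reminder to schedule a date for the follow-up surveys", without limiting this to one arm.

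On size, the trial "will be conducted in 12 (4 in each group) of the 53 churches in the diocese", and "we made a pragmatic decision to select 12 churches for the study and 25 participants per church".

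Outcome measures and Quantitative data analyses plan recruitment and retention rates, effect sizes, variances and 95% confidence intervals for differences between arms. These are to feed the sample size of a definitive trial. The Discussion explains that BSS+ was included to learn whether faith-based messages are feasible and may strengthen or prolong the effect of the adapted intervention.

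**The concern.** An eligibility rule that depends on the allocated arm creates an imbalance that randomising churches cannot remove, because the rule itself produces it. A member without a qualifying phone can enter a BSS or control church but not a BSS+ church. Three groups of results are exposed.

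- **Effect sizes.** BSS+ versus BSS is the contrast that isolates the messages. It would mix the effect of the messages with the effect of leaving out non-owners. BSS+ versus control has the same problem.
- **Recruitment.** The proportion of screened people who are eligible has a different meaning in BSS+.
- **Retention.** Reminders go by text and telephone in every arm, but only in BSS+ is every participant known to have a phone. The protocol intends to note differences in attrition between groups.

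The pilot exists to supply inputs for a larger trial. If the rule is carried forward, the larger trial would estimate the same bias with more precision.

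**Working it through.** The protocol gives no power calculation to reproduce. Its sample size is a pragmatic choice: 3 × 4 = 12 churches, 12 × 25 = 300 participants, 4 × 25 = 100 per arm.

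**Inputs**
- Ownership p. The Background gives subscribers equal to an estimated 87% of the national population. This is a proxy, not ownership among adult churchgoers in Lagos. Assumed range: 70% to 95%.
- Difference d between owners and non-owners on an outcome, in SD units. Not in the document; assumed 0.2, 0.5 or 1.0.
- Retention: 80% in owners (the protocol's 6-month target) and an assumed 60% in non-owners.
- ICC: not stated; assumed 0.01, 0.05 or 0.10.

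**Composition.** At p = 0.87, about 100 × 0.13 = 13 of 100 participants in each of BSS and control would be non-owners, against 0 of 100 in BSS+. The chance that a church of 25 includes at least one non-owner is 1 − 0.87^25 = 0.97.

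**Bias in a BSS+ contrast when the treatment has no effect:** (1 − p) × d.

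| p | d = 0.2 | d = 0.5 | d = 1.0 |
|---|---|---|---|
| 0.95 | 0.01 | 0.03 | 0.05 |
| 0.87 | 0.03 | 0.07 | 0.13 |
| 0.70 | 0.06 | 0.15 | 0.30 |

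**Retention gap from eligibility alone:** (1 − p) × (80 − 60) points = 1.0 at p = 0.95, 2.6 at p = 0.87 and 6.0 at p = 0.70.

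**Eligible proportion.** If the arms are otherwise alike, the proportion eligible in BSS+ is p times that in the other arms, so 0.87 times at the proxy value.

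**Sampling error for scale.** The standard error of an arm difference in SD units is √(2 × (1 + 24 × ICC)/100).
- ICC 0.01: √(2 × 1.24/100) = 0.16
- ICC 0.05: √(2 × 2.2/100) = 0.21
- ICC 0.10: √(2 × 3.4/100) = 0.26

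For retention near 80%, multiplying the variance by 0.8 × 0.2 = 0.16 gives standard errors of about 6.3, 8.4 and 10.4 percentage points.

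The central figures, 0.07 SD and 2.6 points, lie well below one standard error. The bias reaches the size of the sampling error only if ownership is far below 87% or owners differ strongly: 0.30 SD at p = 0.70 and d = 1.0.

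**After the change.** With one criterion in all arms, p = 1 everywhere among those enrolled, so (1 − p) × d = 0 for any d.

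**The case against.** Much can be said for the protocol.

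- **The rule has an obvious reason.** Only BSS+ delivers text messages as an intervention. That stands: the rule is not arbitrary. It explains why BSS+ needs phones, but does not justify unequal eligibility.
- **The statement on recruitment may concern procedure only.** A reader might infer a flat contradiction with the eligibility section. The surrounding text is about announcements, bulletin inserts and order of arrival, and it makes recruitment subject to eligibility. The two sections sit uneasily together, but a procedural reading is possible.
- **Phones are not shown to be needed in every arm.** Table 1 lists "Motivational interviewing phone calls delivered to participants by trained volunteer peer counselors" for BSS too, and a reader might infer that every BSS participant needs a phone. The text under supportive relationships limits the calls to selected members. Two or three counselors with at least five participants each gives a minimum of 10 to 15 of 25. A voice call also does not need a text-compatible phone used for 6 months. If phones were needed in practice everywhere, few non-owners would enrol and the imbalance would shrink.
- **Retention may not suffer.** Participants attend at least weekly and surveys are mainly completed at church, so non-owners can be reached in person. Bias in favour of BSS+ is possible, not established.
- **The messages are also assessed in other ways:** proportions received, opened and read, participant ratings and focus groups. None of these needs the BSS arm.
- **No significance tests of change are planned on the outcomes,** and no success indicator is a contrast between arms. The harm is confined to estimates carried forward.
- **Reasons for non-eligibility are already to be recorded.** Only reporting them by arm is not explicit.

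These points limit the size and urgency of the problem. None makes the BSS+ contrasts like with like.

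**Conclusion.** The point holds for the two BSS+ contrasts and the proportion eligible, and possibly for retention. A reader might infer that the three arms enrol three different populations. They do not: BSS and control have identical criteria, so there are two populations and BSS versus control is untouched. The mechanism is differential eligibility after cluster allocation, a form of selection bias.

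Its size and direction are unknown. The central figure of about 0.07 SD, with a range of 0.03 to 0.15 SD, rests on the subscriber proxy, an ownership range of 70% to 95% and an assumed 0.5 SD difference. The 2.6-point retention gap rests on an assumed 20-point deficit in non-owners. Both central figures are probably below the pilot's sampling error.

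The existence of the bias is certain from the text if any non-owner who differs from owners enrols in BSS or control; its magnitude is not. It should be fixed because it is systematic, cannot be repaired afterwards unless ownership is recorded in every arm, and would pass into the definitive trial. It is not large enough to undermine the pilot's feasibility aims.

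**What to change.** Apply the same phone criterion (text-compatible, used for at least 6 months) to participants in all three arms, and report by arm the number excluded for lack of a phone. That count is itself a useful feasibility result.

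Alternatively, keep the wider entry to BSS and control, record phone ownership by the same definition at screening and baseline in every arm, and restrict BSS+ contrasts, including retention and the proportion eligible, to owners.

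In either case, reconcile the eligibility section with the statement on recruitment under Recruitment and retention strategies.

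**Cost.** The first option changes one line in the criteria and the screening form. BSS and control become slightly less general. To enrol 25, each church needs about 25/0.87 = 28.7 otherwise eligible members at 87% ownership (26.3 at 95%, 35.7 at 70%), as BSS+ churches already do. The total of 300 is unchanged. The second option keeps wider entry but leaves about 87 of 100 participants per comparison arm for BSS+ contrasts at 87% ownership.
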